### Sample and Eligibility Criteria

The sample consists of 439 caregiver-child dyads living in 3 cities in Azerbaijan: Baku, Sumgait, and Ganja. Caregivers and children must meet the eligibility criteria to participate and commit to study participation to be enrolled. Eligible children (1) are 7 to 12 years old at baseline, (2) have a history of institutionalization (for at least 1 month), and (3) have been reunited with a caregiver (biological parent or kin relative) within a year before the start of the study.

Eligible caregivers (1) are a biological parent or kin relative (eg, grandparent) who serves as the primary caregiver;, (2) reunified with the child before the study, and (3) are at least 18 years old at baseline. Children or caregivers with significant cognitive, behavioral, and/or mental health impairment (eg, severe developmental disorder) that may interfere with their ability to consent to, benefit from, or participate safely in the program are excluded from participation. More than 1 eligible child in a family may be enrolled in the study. Enrollment requires consent from the caregiver and assent from the child (see Multimedia Appendix 1 for sample consent and assent forms).

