### Randomization

The principal investigator (PI) conducted the randomization prior to the start of recruitment. Eight computer-generated random numbers (ranging from 0 to 100) were assigned to the 8 intervention conditions and ranked from lowest to highest to determine the allocation sequence within each city. The first 5 families recruited in a city were assigned to the first intervention condition in the sequence. After 5 families had been assigned to each intervention condition, allocation resumed at the beginning of the sequence. To reduce predictability, the random numbers were generated from a range of 0 to 100 rather than 1 to 8. A secure, web-based, password-protected database was used to maintain the randomization record.

Data collectors were masked to participants’ intervention group assignments. To foster fidelity to the intervention manuals and maintain the integrity of each separate intervention, facilitators delivered only 1 type of intervention and were not trained in the specific content of the other intervention strategy. Due to the nature of the recruitment procedures, participants could not be blinded to the existence of other intervention conditions.

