Aim 1: To estimate the effects of intervention components on child mental health outcomes, differences in outcomes (eg, depression score) will be tested across 3 time points (baseline, 1 year, and 2 years), under an intent-to-treat basis, using linear mixed models. This approach accounts for the autocorrelation of observations nested within individuals over time. We will use logistic functions for binary outcomes (eg, mental health symptoms above the clinical cutoff), Poisson or negative binomial functions for count outcomes (eg, the number of aggressive behaviors), and linear functions for continuous variables (eg, self-esteem score). Statistical inference will be based on F-statistics and their associated *P* values for between-subject effects (the intervention assignment × time terms). To estimate the main effects for the 3 intervention components, we will determine if there is a difference in change across time using the baseline as the reference point (eg, 1 year vs baseline; 2 years vs baseline). We will also include 2-way interactions between components (eg, Family Strengthening by Economic Empowerment by Time interaction). Since we will use effect (–1, 1) coding rather than dummy (0, 1) coding, the power for tests of main effects and interactions will be identical for similarly sized effects. Covariates will include baseline attributes for outcome variables (eg, child’s age and gender, caregiver characteristics).Aim 2: To test which intervention component is mediated by hypothesized mediators, including (1) supportive parenting (eg, quality of child-parent relationships), (2) emotion regulation (eg, self-regulation), and (3) parental stress (eg, stress response). We will use a 2-step process [61] to test (1) a measurement model using confirmatory factor analysis that examines the relationships between the latent constructs and their indicator variables and (2) a structural model to test the hypothesized relationships between the latent mediating and outcome constructs and the intervention [62]. We will use the maximum likelihood method of parameter estimation with missing data. We will also conduct separate analyses to examine the effectiveness of intervention components in specific subgroups (eg, by gender).Aim 3: Qualitative analysis will be conducted in both Azerbaijani and English to explore barriers and facilitators to intervention participation and implementation. Bilingual investigators and 2 additional coders will independently review interview transcripts and conduct thematic analysis [63] and content analysis [64] using Dedoose [65]. Analyses will assess themes and concepts regarding participants’ and intervention facilitators’ perspectives on mental health needs, intervention engagement and acceptability, changes in family relationships and dynamics, and contextual and sociocultural factors influencing intervention delivery and outcomes.

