
In the data analysis, the primary outcomes include children’s mental health and socioemotional functioning. Secondary outcomes include cognitive and social processes associated with mental health, as well as functional outcomes related to academic performance and social functioning in the school setting. Specifically, primary mental health outcomes include child-reported depressive symptoms, posttraumatic stress symptoms, and self-esteem; caregiver- and teacher-reported ADHD symptoms and general socioemotional functioning such as internalizing and externalizing problems; and clinician-administered mental health outcomes among families randomized to the mental health services condition. Secondary outcomes include child cognitive functioning, assessed using WISC-V and CANTAB tasks; child-reported social support, particularly peer support; and teacher-reported grades and school behaviors. Mediating variables include caregiver-reported parenting practices, caregiver mental health, family functioning, coping strategies, social support, saving attitudes, and household economic well-being.

The main analyses focus on treatment effects at the 1-year and 2-year follow-ups, with the 1-year follow-up used to assess initial intervention effects and the 2-year follow-up used to assess the maintenance of those effects over time. Children from the same family will be accounted for using mixed-effects models, with random effects specified to adjust for the nonindependence of observations among children nested within the same family. Missing outcome data will be handled using maximum-likelihood estimation under a missing-at-random assumption, with sensitivity analyses using multiple imputation. To address the multiple testing issue, we will control the false discovery rate using the Benjamini-Hochberg procedure [66,67]. This approach was selected instead of Bonferroni correction because it limits false discoveries while avoiding the overly conservative loss of power associated with Bonferroni adjustment when multiple related hypotheses are tested.

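### Allocation is organised within three cities, but city is not named in the stated Aim 1 model; the cost is a small loss of precision

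*Protocol article*

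**What the plan says.** The sample comes from families "living in 3 cities in Azerbaijan: Baku, Sumgait, and Ganja" (Sample and Eligibility Criteria). Under Randomization, eight random numbers are attached to the eight conditions and "ranked from lowest to highest to determine the allocation sequence within each city". Allocation then proceeds in runs: "The first 5 families recruited in a city were assigned to the first intervention condition in the sequence", and so on through the eight conditions before returning to the start. City is therefore the stratum, and the family is the unit allocated.

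The Analytical Strategy describes the Aim 1 model in some detail. The tested terms are component x time, read as change from baseline: "we will determine if there is a difference in change across time using the baseline as the reference point". Two-way component interactions and effect coding are specified. On covariates it says: "Covariates will include baseline attributes for outcome variables", followed by examples marked eg: the child's age, the child's gender and characteristics of the caregiver. On correlation it names the child ("This approach accounts for the autocorrelation of observations nested within individuals over time") and the family ("random effects specified to adjust for the nonindependence of observations among children nested within the same family"). City or site does not appear as a covariate, fixed effect or random effect, and it is not among the moderators in Table 2.

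**The concern.** An analysis should normally carry the factor by which the trial allocated. When allocation is roughly balanced within city, the component estimate is nearly the same with or without city in the model, but the standard error is not. Without city, between-city variation in change is counted as noise although the design has already removed it from the comparison. The standard error comes out too large and some power is given away.

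The second issue is balance itself. One full cycle is 8 conditions x 5 families = 40 families. A city that stops partway through a cycle has a surplus in the conditions that come early in its order. A component's on and off halves can then differ in city mix, and without a city term that difference stays in the estimate.

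**Working it through.** **Inputs from the article.** Three cities; eight conditions; five families per run; inference on component x time from baseline; two-sided alpha 0.05 and power 0.80 (Power Calculations); 305 caregivers and 439 children enrolled (Results). The article gives no city sizes, no city effect and no share of variance due to city, so these are assumed below. The detectable range of 0.09 to 0.12 in Power Calculations is not used here.

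**1. Loss from leaving city out.** Let R² be the share of variance in change explained by city. With balance within city, the standard error without city is too large by the factor 1/√(1 − R²). If the city-adjusted test has 80% power, then

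- power without city = Φ(1.960 + 0.842 − 1.960/√(1 − R²))
- true two-sided alpha without city = 2Φ(−1.960/√(1 − R²))

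| Assumed R² | SE factor | Power without city | True alpha |
|---|---|---|---|
| 0.01 | 1.005 | 79.7% | 0.049 |
| 0.02 | 1.010 | 79.4% | 0.048 |
| 0.05 | 1.026 | 78.5% | 0.044 |
| 0.10 | 1.054 | 76.9% | 0.039 |
| 0.15 | 1.085 | 75.0% | 0.034 |

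For R² = 0.10: 1.960/√0.90 = 2.066, 2.802 − 2.066 = 0.736, and Φ(0.736) = 0.769.

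The described allocation was also simulated, incomplete cycles included: 305 families, an assumed split of 160/80/65, and 4,000 runs per setting. Power without and with city was 0.801 and 0.808 (R² = 0.02), 0.800 and 0.817 (0.05), and 0.810 and 0.845 (0.10). Under the null, rejection without city was 0.044, 0.054 and 0.044, with a Monte Carlo standard error of √(0.05 × 0.95/4000) = 0.0034. It was never above the rate with city in the model. There is no sign of inflation.

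**2. Are incomplete cycles certain?** Take the 305 caregivers as 305 families. If every city had finished on a full cycle, the total would be a multiple of 40. Since 305 = 7 × 40 + 25, at least one city stopped partway.

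**3. Size of the chance imbalance.** Assume 165/80/60 families.

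- The city of 80 is balanced for any component (40 on, 40 off).
- The city of 165 has one surplus run, giving 85 against 80.
- The city of 60 has four surplus runs. If k of these four conditions have the component on, it has 20 + 5k families on and 40 − 5k off. With a random order, k = 0 to 4 has probabilities 1, 16, 36, 16 and 1 out of 70.

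The absolute on/off difference in the smallest city's share, averaged over which side gets the surplus run in the city of 165, is:

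- k = 2: 30/150 − 30/155 = 0.006
- k = 3 (k = 1 mirrors it): 35/160 − 25/145 = 0.046 or 35/155 − 25/150 = 0.059, average 0.053
- k = 4 (k = 0 mirrors it): 40/165 − 20/140 = 0.100 or 40/160 − 20/145 = 0.112, average 0.106

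Mean = (36 × 0.006 + 32 × 0.053 + 2 × 0.106)/70 = 0.030. The maximum, 0.112, occurs with probability 1/70.

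If change in that city differs from the others by an assumed 0.3 SD, the estimate moves by 0.030 × 0.3 = 0.009 SD on average and by at most 0.112 × 0.3 = 0.034 SD. Both scale in proportion to the assumed city difference.

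For the 160/80/65 split, the same reasoning (five surplus runs in the smallest city) gives differences of 35/155 − 30/150 = 0.026 with probability 48/56 and 40/160 − 25/145 = 0.078 with probability 8/56. The mean is 0.033 and the maximum 0.078, or 0.010 and 0.023 SD. Further assumed splits gave means of 0.007 to 0.033 and maxima of 0.02 to 0.14; times 0.3, that is 0.002 to 0.010 SD on average and 0.006 to 0.042 SD at the extreme.

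**The case against.** The strongest reply is that the covariate list is introduced by an eg and is therefore open. City is known at enrolment and could be among the unlisted covariates, and a condensed article commonly leaves the full list to an analysis plan that is not shown here. This stands in part. A reader might infer that city is excluded or that the model ignores its stratum, and the text does not support that: no sentence excludes city or calls the list complete. What can be said is that city is not named, that every covariate example is at person level, and that the article gives sibling clustering its own sentence but says nothing of the allocation stratum.

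A reader might also infer that incomplete cycles bias the component effects. They do not. The order of conditions is random, so the imbalance is zero in expectation. A city difference that is constant over time largely cancels in change from baseline; only city differences in change matter. Nor is type I error inflated: the omission errs on the conservative side.

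Two further points are fair. The article does not settle whether each city had its own random order or one order was reused; the simulation and the averages above assume independent orders. With one reused order, k = 4 forces the surplus run in the city of 165 onto the same side, and the 165/80/60 maximum becomes 40/165 − 20/140 = 0.100. City is the stratum either way. And the change is not wholly free of consequence: in the logistic models, conditioning on city alters the odds ratio being estimated.

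**Conclusion.** The point holds as a minor one. Allocation is organised by city, and the Aim 1 model as described does not name city. Fitted that way, it gives up about 0.3 to 3 power points for an assumed city R² of 0.01 to 0.10. It also leaves unadjusted a chance imbalance worth about 0.01 SD on average and up to about 0.03 SD, given the 165/80/60 split and a 0.3 SD city difference in change. All of these sizes rest on assumed city sizes and city effects, and the imbalance is counted in families, not children. The loss is one of precision; the validity of the component tests is not in question.

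**What to change.** State in the Analytical Strategy that city and city x time enter the Aim 1 models as fixed effects, alongside the covariates already listed. City x time is the term that matters, because the tests concern change from baseline. With three cities this uses 2 degrees of freedom per wave and only data already held.

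Follow-up is complete and the effect analyses are under way, so the choice should be fixed before they are finished and declared openly as a clarification of the plan. Otherwise, adjusting for city becomes a decision taken with outcome data in view. For the binary outcomes, note that the odds ratio is conditional on city. If an analysis plan already includes city, one clause in the article confirming it is enough.

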## Methods

### Study Design

This randomized clinical trial used a full 2³ (2×2×2) factorial design based on the multiphase optimization strategy (MOST) framework to test and compare three intervention approaches: (1) a family-strengthening intervention, (2) trauma-focused child mental health services, and (3) asset-based economic empowerment via Child Development Accounts (CDAs).

Multicomponent interventions are often tested as “bundles,” making it difficult to disentangle the contributions of individual components. The MOST is a systematic method that allows for the testing of the independent effects of different intervention components to identify their most optimal combination [15]. While multiarm randomized controlled trials are costly, often limited in arms, and require larger sample sizes, the MOST uses a factorial design. By comparing combinations of experimental conditions, the study can have a greater number of conditions without a substantial increase in sample size. This is advantageous in LMICs, where it is essential to implement only the most efficacious aspects of a program. The MOST consists of three phases: (1) preparation, (2) optimization, and (3) evaluation of the optimized intervention in a randomized controlled trial [16]. This study falls within the optimization phase.

This study includes 3 factors—the intervention approaches—each with 2 levels (delivered/“on” or not delivered/“off”). This is a full 2×2×2 factorial design, meaning that the study has 8 different experimental conditions or groups (2^3^=8) [17]. Child-parent dyads (n=439) were randomly assigned to 1 of 8 groups (about 54 dyads per group), which determined the combination of interventions they received. Given this design, half of the sample (n≈220) received each intervention (eg, families assigned to groups 1‐4 received the family-strengthening intervention and were compared with families from groups 5‐8; Table 1).

**Table 1. T1:** Experimental conditions^a^.

Group	Usual care	Experimental interventions		
	Standard deinstitutionalization program	Family strengthening	Trauma-focused mental health services	Economic empowerment
1	On	On	On	On
2	On	On	On	Off
3	On	On	Off	On
4	On	On	Off	Off
5	On	Off	On	On
6	On	Off	On	Off
7	On	Off	Off	On
8	On	Off	Off	Off

a Child-parent dyads (n=439) are randomly assigned to 1 of 8 experimental conditions (~54 dyads per group), determining how many and which intervention components participants receive.

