### Intervention Quality Assurance and Implementation Measures

For each component, we will analyze data regarding participation (eligibility, enrollment, and attrition rates), intervention fidelity (via facilitator and participant rating forms completed at the end of each session), safety (number of adverse events), intervention acceptability (participant satisfaction, session attendance, and associations between satisfaction and attendance), perceived usefulness (relevance and utility), and cross-arm contamination.

Two interim analyses will be conducted when 33.3% and 66.7% of the planned sample size have completed 6-month follow-up assessments. With respect to efficacy, if any interim analysis shows statistical significance (*P*<.05) for all primary outcomes, the study will be stopped, indicating a significant benefit of 1 intervention over another. With respect to futility, if the effect size estimates suggest a null result is likely given the planned total sample size, the study may be stopped to conserve resources. A post hoc power analysis will assess the minimum sample size needed to achieve 80% power *and* reject the null hypothesis at each interim analysis. If this exceeds the planned 400 dyads for self-reported outcomes, the investigative team will discuss whether to stop the study for futility or modify the design to avoid it, such as increasing enrollment or hiring additional staff.

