### Outcome Measures

As presented in Table 2, the primary mental health outcomes include child-reported symptoms of depression (20-item Center for Epidemiological Studies Depression Scale for Children) [41], posttraumatic stress (8-item Children’s Revised Impact of Events Scale) [42], self-esteem (20-item Tennessee Self-Concept Scale-Second Edition) [43], attention-deficit/hyperactivity disorder (ADHD) symptoms (caregiver and teacher-reported 19-item ADHD Rating Scale-IV) [44], and general social-emotional functioning (caregiver and teacher-reported 25-item Strengths and Difficulties Questionnaire) [45]. Grades from school records and teacher-reported school behaviors (eg, completing homework, fights with other students) are also outcomes of interest. The Strengths and Difficulties Questionnaire has been validated in the Azerbaijani language [46]. Child mental health outcomes among families randomized to the mental health services were also assessed by a clinician-administered Health of the Nation Outcome Scales for Children and Adolescents (15 items) [47].

**Table 2. T2:** Measurement instruments^a^.

Outcomes and measurement instrument	Respondent
Outcomes (study aim 1)	
Internalizing and externalizing problems	
Center for Epidemiological Studies Depression Scale for Children	Child
Strengths and Difficulties Questionnaire	Caregiver, teacher
ADHD Rating Scale IV	Caregiver, teacher
Health of the Nation Outcome Scales Child and Adolescent Mental Health	Clinician rated
Traumatic symptoms	
8-item Children’s Revised Impact of Events Scale	Child
Cognitive and executive functioning (attention, cognitive control-response inhibition or impulsivity, working memory)	
*The Cambridge Neuropsychological Test Automated Battery*, a digital battery of nonverbal cognitive tasks to assess motor function, processing speed, working memory, executive functioning, and emotion recognition bias through the Motor Screening Task, Reaction Time, Spatial Span, Stockings of Cambridge, and Emotion Bias Task, respectively. *The Wechsler Intelligence Scale for Children* Block Design and Picture Span subtests to assess nonverbal reasoning and visuospatial working memory, respectively.	Child (Digital paradigm tasks)
Self-concept	
Tennessee Self-Concept Scale-Second Edition	Child
Social support	
Social Support Scale for Children	Child
School performance	
Academic performance (grades), school behaviors	Teacher, admin records (school)
Child-parent mediators (study aim 2)	

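### The clinician-rated scale is listed as a primary outcome but is described only for families assigned to mental health services, so it cannot show the effect of that component

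*Protocol article*

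**What the plan says.** Analytical Strategy divides the outcomes into primary and secondary. Its list of primary mental health outcomes ends with "clinician-administered mental health outcomes among families randomized to the mental health services condition". Table 2 places the scale under the Aim 1 outcomes, as clinician rated.

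Outcome Measures gives a different impression. It opens with the primary outcomes (depression, posttraumatic stress, self-esteem, ADHD symptoms, social-emotional functioning), turns to grades and school behaviors, and then adds: "Child mental health outcomes among families randomized to the mental health services were also assessed by a clinician-administered Health of the Nation Outcome Scales".

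For Aim 1, inference rests on "between-subject effects (the intervention assignment × time terms"). The plan adds: "We will also include 2-way interactions between components". No exception is made for any outcome. Under Study Design the children "were randomly assigned to 1 of 8 groups (about 54 dyads per group"), and "half of the sample (n≈220) received each intervention".

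**The concern.** The purpose of the factorial design is that every component is judged by comparing children who were assigned to it with children who were not. An outcome measured only where one component is on gives no such comparison for that component. All that is left for mental health services on this outcome is change over time within the families who received them, and that cannot separate the intervention from what would have happened anyway.

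The trial exists to compare three components and select among them. A primary outcome that can inform two of them only in half the sample, and the third not at all, does not fit that purpose. The article also leaves the reader unsure whether the scale is primary or supplementary.

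**Working it through.** Below, A is family strengthening, B mental health services and C economic empowerment, following the article's intervention headings.

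**1. The article's own counts.** 439 / 8 = 54.9 children per group and 439 / 2 = 219.5 per component level. These agree with the stated figures of about 54 and about 220. Also 400 × 0.90 = 360, the analyzed number in Power Calculations.

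**2. Where the scale is measured.** In Table 1, B is on in groups 1, 2, 5 and 6 and off in groups 3, 4, 7 and 8. The scale is described for the first set: 4 × 54.9 = 219.5 children. No section describes it for the second set; Data Collection mentions only child, caregiver and teacher surveys for everyone.

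**3. What can be estimated.** With the planned −1/1 coding, the four groups with ratings give these model columns:

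| Group | Intercept | A | B | C | A×B | A×C | B×C |
|---|---|---|---|---|---|---|---|
| 1 | 1 | 1 | 1 | 1 | 1 | 1 | 1 |
| 2 | 1 | 1 | 1 | −1 | 1 | −1 | −1 |
| 5 | 1 | −1 | 1 | 1 | −1 | −1 | 1 |
| 6 | 1 | −1 | 1 | −1 | −1 | 1 | −1 |

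On all eight groups the seven columns have rank 7. On these four the rank is 4. Column B equals the intercept, A×B equals A, and B×C equals C. Multiplying each column by time changes nothing: B by time cannot be told apart from time, A×B by time from A by time, or B×C by time from C by time. A×C can still be estimated.

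**4. What the A and C contrasts mean here.** With B fixed at +1, the coefficient on A is the A effect plus the A×B effect, and the coefficient on C is the C effect plus the B×C effect. Each equals the factorial main effect only if the interaction is zero, which these data cannot test.

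**5. Precision for A and C.** A compares groups 1 and 2 with 5 and 6; C compares groups 1 and 5 with 2 and 6. Each is 219.5 / 2 ≈ 110 against 110, instead of about 220 against 220. The detectable difference grows by √(220 / 110) = 1.41.

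At the planning numbers (two-sided 0.05, 80% power, one time point), the detectable standardized difference is (1.96 + 0.84) × √(2/n):

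- n = 180 per level: 0.295
- n = 90 per level: 0.418

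At a true difference of 0.295, power falls from 80% to about 51%.

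The article's detectable range of 0.09 to 0.12 names neither the effect-size metric nor the autocorrelation. Assume Cohen's f, a between-subject F test with noncentrality N f² m / (1 + (m − 1)ρ), m = 3 and N = 360. Then f = 0.094 at ρ = 0.1 and 0.121 at ρ = 0.5, consistent with that range. At N = 180 these become 0.133 and 0.171, again about 1.4 times larger. Other forms of the test give other values, so the range is not uniquely reproduced; the conclusion does not depend on it.

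**6. Missing-data methods.** Maximum likelihood under missing at random, or multiple imputation, cannot supply the B contrast. With no rated child where B is off, any value there would be pure extrapolation from the model.

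**The case against.** The strongest reply is that the restriction is stated openly and the harm is small. Depression, posttraumatic stress, self-esteem, and caregiver- and teacher-reported ADHD symptoms and social-emotional functioning are not limited by condition, so B is estimable on all of them and the choice of components need not depend on HoNOSCA. Outcome Measures suggests a supplementary role. No section says that within-arm change will be offered as evidence for B. All of this stands. It limits the point to one outcome, but leaves that outcome listed as primary with a planned analysis the design cannot deliver.

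A reader might infer more than the article supports:

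- **Masking is broken.** The article states "Data collectors were masked" and does not say who rates the scale. Intervention B says the treating clinicians took no part in research activities. Knowing that B is on does not reveal A or C, and there is no comparison between levels of B to bias.
- **Regression to the mean is shown by the 52% above the depression cutoff.** Enrolment was on age, institutional history and reunification, not on symptom scores, and the 52% comes from a different, child-reported scale.
- **The Benjamini-Hochberg procedure is filled with inestimable tests.** A term that cannot be estimated yields no P value to enter.
- **The interim efficacy rule cannot work for B.** That rule says that on significance "for all primary outcomes, the study will be stopped". Recruitment and follow-up are complete, so no stopping decision remains to be affected.

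**Conclusion.** The concern holds for this one outcome. As written, Analytical Strategy makes HoNOSCA primary, yet on it the B effect and the A×B and B×C interactions are not identified at any sample size. A and C are estimable on about 110 against 110 children, with a detectable difference about 1.41 times larger, and only as effects conditional on B being on. Outcome Measures and Analytical Strategy also need to agree on the scale's status.

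This rests on reading the scale as collected only where B is on. The article does not use that word, but both descriptions are restricted to those families and nothing describes it elsewhere. The sample-size figures assume equal groups. The power figures ignore siblings within families, as a simple two-group calculation does. The finding does not mean that the trial cannot evaluate mental health services.

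**What to change.** In Analytical Strategy, take HoNOSCA out of the primary outcomes, and so out of the set of primary tests over which the false discovery rate is controlled. Wording along these lines would do:

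> HoNOSCA was rated only in the four conditions that include mental health services. It is reported descriptively in those conditions. Contrasts of family strengthening and economic empowerment on it are exploratory and apply only where mental health services are provided. Change on it within these conditions is not taken as evidence for mental health services, which are evaluated only on measures collected in all eight conditions.

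Bring Outcome Measures and Table 2 into line with this. If the scale was in fact rated in all eight conditions, correct both descriptions instead.

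The cost is a few sentences, no new data and one fewer primary measure. Data collection is complete and the effect analyses are ongoing, so the change should carry a date and a reason. It should also state that it was made before the effect results were known, or say plainly if it was not.
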